## Abstract

*Introduction*. Retrospective observational data show that ACE-inhibitor therapy delays renal failure and improves life expectancy in Alport patients with proteinuria. The EARLY PRO-TECT Alport trial assesses the safety and efficacy of early therapy onset with ramipril in pediatric Alport patients. *Methods and analysis*. This double-blind, randomized, placebo-controlled, multicenter phase III trial (NCT01485978; EudraCT-number 2010-024300-10) includes 120 pediatric patients aged 24 months to 18 years with early stages of Alport syndrome (isolated hematuria or microalbuminuria). From March 2012, up to 80 patients will be randomized 1:1 to ramipril or placebo. In the event of disease progression during 3-year treatment, patients are unblinded and ramipril is initiated, if applicable. Approximately 40 patients receive open-label ramipril contributing to the safety database. Primary end-points are “time to progression to next disease level” and “incidence of adverse drug events before disease progression.” Treatment effect estimates from the randomized comparison and Alport registry data will be combined in supportive analyses to maximize evidence. *Conclusion*. Without this trial, ACE inhibitors may become standard off-label treatment in Alport syndrome without satisfactory evidence base. The results are expected to be of relevance for therapy of all pediatric patients with kidney disease, and the trial protocol might serve as a model for other rare pediatric glomerulopathies.

## 1. Background

More than two decades have passed since the identification of COL4A5 gene as the genetic locus for X-linked Alport syndrome (AS) [1]. The hereditary type IV collagen disease Alport syndrome leads to progressive kidney fibrosis and end-stage renal failure. Knowledge of the mutation has allowed early genetic diagnosis [1] of AS years or even decades before renal failure. Still, despite early diagnosis, no evaluated therapy could be offered until recently.

Animal studies on AS, based on the fundamental genetic discoveries, have produced a variety of potentially effective therapies for Alport kidney disease [2–5]. In “Alport-mice,” early therapy onset with the angiotensin-converting-enzyme-inhibitor (ACEI) ramipril doubled the lifespan until renal failure [5]. This basic research results have led ACEIs to be the standard off-label therapy of AS for most nephrologists, including pediatric nephrologists. Retrospective observational data have shown that ACEIs reduce proteinuria [6] and, most important, delay end-stage renal failure and thus improve life expectancy in Alport patients [7]. The data show the efficacy of ACEI treatment of AS patients with proteinuria (and to a lesser extent in patients with ongoing renal failure). To date, no serious side effects of ACEIs have been reported to the North American or European Alport syndrome registries. However, retrospective registry data do not guarantee the comprehensive reporting of serious adverse events (SAEs) and adverse drug reactions (ADRs). ACEIs are not authorized for use in children with proteinuria or any type of renal disease [8, 9]. ACEIs are currently authorized for use in hypertensive children aged 8 years and older. No controled clinical trial has ever assessed the safety and efficacy of ACEIs in pediatric AS patients. Safety data from adults are poorly predictive for children. Thus, decisions on the off-label treatment of children with AS are currently made by the treating pediatrician.

The prospective, randomized EARLY PRO-TECT Alport trial was planned to provide valid data as the basis for a treatment recommendation and a subsequent marketing authorization for ramipril in children with AS. Without this trial, ACEIs may become the de facto standard off-label treatment of Alport syndrome without satisfactory evidence base.

## 2. Methods and Analysis

### 2.1. Design

EARLY PRO-TECT Alport is a phase III, multicenter, randomized, placebo-controlled, double-blind (patient, investigator and trial team http://www.clinicaltrials.gov/) clinical trial conducted in Germany according to the German Medicines Act (Arzneimittelgesetz). Up to 80 previously untreated AS patients with Alport stages 0 or I at screening (Table 1) will be randomized into once-daily treatment over 3 years with ramipril or placebo. Patients will be randomized (stratified by trial site) at a 1 : 1 ratio using permutated blocks (Figure 1). Upon disease progression (Table 2) during the treatment period, patients are unblinded, and ramipril treatment is initiated, if applicable. Approximately 40 AS patients will be treated open label with ramipril and will contribute to the safety database. This group includes previously treated as well as untreated patients who or whose parents/legal guardian refuses randomization because they request treatment.

### 2.2. Participants

Patient eligibility criteria are listed in Table 3. This trial includes patients with very early stages of AS (before proteinuria >0.3 g per day). As most pediatric nephrologists (>90%) today already treat AS children with proteinuria and/or renal impairment (unpublished data in [4]), not enough untreated AS patients at the stage of proteinuria would be available for a controlled clinical trial.

All newly diagnosed patients in Germany (or from outside Germany who are willing to travel to Germany) will be assessed for eligibility over the recruitment period of 2 years. Recruitment will be supported by the German and other national Alport patients' advocacy groups. The trial is supported by the Study Group of the German Society of Paediatric Nephrology.

### 2.3. Intervention

Over the treatment period of three years, randomised patients receive once-daily ramipril and placebo, respectively. For previously untreated patients, ramipril will initiated at 1 mg/m^2^ and uptitrated by 1 mg/m^2^ every 2 months over the first 10 months until the individual maximum tolerated dose (MTD) has been reached (Figure 2). 

For the open-label treatment group, patients who are pretreated with another ACEI before study entry will change treatment to ramipril within two weeks prior to the study-specific first dosing occasion. For patients under 18 years of age, the maximum daily dose of ramipril will be 6 mg/m^2^. From the age of 18 years, the maximum daily dose of ramipril will be 10 mg. After completion of the treatment period, treatment may be continued or initiated at the investigator's discretion and the patient's and/or parents'/guardians' wish. Ramipril was chosen as ACE inhibitor, because of the preclinical data in Alport mice [5] and clinical data in hypertensive children in the ESCAPE trial [8].

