## 3. Discussion and Conclusion

ACE-inhibitor therapy in AS patients with proteinuria reflects the common off-label treatment [7]. However, long-term therapy with ACEIs in children may lead to long-term drug toxicities unknown in adults. This makes long-term off-label therapy an ethical distress for the pediatric nephrologist. Indications for initiation of treatment by pediatric nephrologists include hematuria alone (3%), microalbuminuria (27%), and overt proteinuria (70%) [4]. Children with AS and proteinuria are thus being treated in a way that prevents the objective assessment of the risks and benefits of therapy. A placebo-controlled clinical trial in children who have not yet developed overt proteinuria is therefore believed not to conflict with the current treatment practices of most pediatric nephrologists [4].

The primary aim of the EARLY PRO-TECT Alport trial is to assess drug safety and efficacy of ramipril treatment in oligosymptomatic pediatric AS patients in the setting of a prospective, placebo-controlled, GCP-conform clinical trial. An integrated translational program will help to define markers of renal disease progression that indicate risk, prognosis, disease activity, and response to therapy without the need for blood sampling or renal biopsy. The results are expected to be of relevance for almost all glomerular renal diseases. Finally, to maximize the available evidence, we will combine the treatment effect estimates from the randomized comparison and Alport registry data. This multimodal concept may serve as a model for other rare pediatric renal diseases, for which trials are similarly difficult to perform.

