**Figure 2 fig2:**
[figure not shown]
Study visits for the individual patient during the EARLY PRO-TECT Alport.

**Table 1 tab1:** Alport syndrome levels describing renal damage and loss of function.

Stage	Definition
0	Microhaematuria without microalbuminuria (usually at birth)
I	Microalbuminuria (30–300 mg albumin/gCrea)
II	Proteinuria >300 mg albumin/gCrea
III	>25% decline of normal renal function (creatinine clearance)
IV	End-stage renal failure (ESRF)

**Table 2 tab2:** Alport syndrome disease progression in this trial.

Progression	Definition
Stage 0 to I	Albuminuria >30 mg albumin/gCrea in combination with a 3-fold increase from baseline in albuminuria, confirmed within 2 weeks.
Stage I to II	(i) Twofold increase from baseline albuminuria, confirmed within 2 weeks
	(ii) Albuminuria >300 mg albumin/gCrea at a single assessment.

**Table 3 tab3:** Patient eligibility criteria.

	*Inclusion criteria*
	(i) Males or females of any ethnic origin aged between 24 months and <18 years at screening. Female patients of child-bearing potential test negative for pregnancy test and agree to use a reliable method of birth control during the study.
	(ii) Definitive diagnosis of Alport syndrome by kidney biopsy (in patient or other affected family members) and/or genetic testing (hemizygous males with X chromosomal Alport syndrome or homozygous males or females with autosomal recessive Alport syndrome) including screening for clinical diagnostic criteria (hematuria, family history of kidney disease, hearing loss, ocular changes).
	(iii) Alport syndrome stages 0 or I.
	(iv) Previously untreated with ACEIs (patients taking an ACEI for the treatment of Alport syndrome may be included in the open-label treatment arm).
	(v) Written informed consent.

	*Exclusion criteria*
	(i) Uncertain diagnosis or variants of Alport syndrome such as heterozygous carriers.
	(ii) Alport syndrome stages II, III, or IV.
	(iii) Known allergies or intolerances to ramipril or related compounds.
	(iv) Known contraindication for ACEI therapy (e.g., bilateral renal artery stenosis, prior history of angioedema, previous hyperkalemia, or previous acute prerenal renal failure).
	(v) Females with a positive pregnancy test or females who are lactating.
	(vi) Additional other chronic renal, liver, or cardiac diseases.
	(vii) No written informed consent.

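### The under-18 dose ceiling has no absolute limit, so a minor above 1.67 m² may receive more ramipril than the trial's own adult maximum of 10 mg

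*Protocol article*

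**What the plan says.** Section 2.3 (Intervention) of the protocol article gives two maximum daily doses in adjacent sentences. For minors: "For patients under 18 years of age, the maximum daily dose of ramipril will be 6 mg/m^2". For adults: "From the age of 18 years, the maximum daily dose of ramipril will be 10 mg". The first is scaled to body surface and has no limit in mg; the second is a limit in mg and is not scaled. No other part of the article caps the under-18 dose in mg.

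The same section starts previously untreated patients at 1 mg/m² and has them "uptitrated by 1 mg/m^2^ every 2 months over the first 10 months until the individual maximum tolerated dose (MTD) has been reached".

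Three other statements determine who falls under these rules:

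- Table 3 admits "Males or females of any ethnic origin aged between 24 months and <18 years at screening", with no limit on body size.
- Section 2.1 says that patients "will be randomized into once-daily treatment over 3 years with ramipril or placebo", so older adolescents can turn 18 on treatment.
- Section 3 warns that "long-term therapy with ACEIs in children may lead to long-term drug toxicities unknown in adults".

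**The concern.** The two ceilings apply to different ages, so they do not contradict each other. They are not aligned, however. Above a certain body surface, the rule for minors permits a higher dose than the rule for adults. A large 17-year-old could be on a dose that the same person may not take at 18, and would have to reduce it on the birthday although it was tolerated.

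What is at stake is patient safety and a coherent dosing rule. Section 2.3 bases the choice of ramipril on mouse data and on a trial in hypertensive children, but it does not explain why minors should be allowed more than adults. The article's own remarks about long-term use in children point towards caution. The primary efficacy endpoint, the sample size and the analysis are not affected.

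**Working it through.** **Inputs from the article**

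- Under-18 ceiling: 6 mg/m² (section 2.3)
- Ceiling from 18 years: 10 mg (section 2.3)
- Titration: start at 1 mg/m², add 1 mg/m² every 2 months for 10 months (section 2.3)
- Age at screening: 24 months to under 18 years (Table 3)
- Treatment period: 3 years (sections 2.1 and 2.3)

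**Assumed.** The article gives no body sizes. Body surfaces of 1.8, 1.9 and 2.0 m² are used for illustration, meaning the value on which the dose is based.

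**Step 1: does the titration reach the stated ceiling?** There are 10/2 = 5 steps, so the top dose is 1 + 5 × 1 = 6 mg/m² at month 10. This reproduces the stated under-18 maximum. The ceiling is where the schedule ends for any patient who tolerates every step.

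**Step 2: where do the ceilings meet?** 10 mg ÷ 6 mg/m² = 1.67 m². Below this the under-18 limit is the lower of the two; above it, the higher.

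**Step 3: excess over 10 mg, and the cut at 18.** Permitted dose = 6 × body surface. Excess = dose/10 − 1. Cut = 1 − 10/dose.

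| Body surface (assumed) | Permitted under 18 | Excess over 10 mg | Cut at 18 |
|---|---|---|---|
| 1.8 m² | 10.8 mg | 8% | 7.4% |
| 1.9 m² | 11.4 mg | 14% | 12.3% |
| 2.0 m² | 12.0 mg | 20% | 16.7% |

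**Step 4: what body size is this?** By the Mosteller formula, √(height in cm × weight in kg / 3600), with assumed heights and weights:

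- 165 cm, 55 kg: 1.59 m², 9.5 mg (below the adult limit)
- 170 cm, 60 kg: 1.68 m², 10.1 mg
- 180 cm, 75 kg: 1.94 m², 11.6 mg

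**Step 5: if the tolerated dose is lower.** At 5 mg/m² the 10 mg mark is passed only above 10/5 = 2.0 m²; at 4 mg/m², only above 10/4 = 2.5 m².

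**Step 6: who would face the cut at 18 on treatment?** Take a previously untreated patient who starts ramipril at entry and whose body surface is between 1.67 and 2.0 m². The 18th birthday must fall within the 3 years, so entry is at 18 − 3 = 15 years or later. The full 6 mg/m² must be reached first, so entry is no later than 18 years − 10 months = 17 years 2 months. That window lies inside the eligible age range. Patients on 10 mg or less at 18 need no change.

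**The case against.** The strongest reply is that this is a condensed article. Section 2.3 summarises dosing in a few sentences, and the full protocol may hold a cap in mg, rounding rules and instructions for an 18th birthday. That would settle the matter if the article were merely silent. It is not silent: it states the maximum for minors, and anyone who follows that statement exactly can exceed 10 mg. If the full protocol has a cap, the published sentence is wrong as a statement of the maximum. If it has none, the dosing rule needs one.

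A second reply is that dosing is individual. Titration goes only as far as the patient tolerates, and section 2.6 schedules six-monthly safety assessments. These are real safeguards, but neither holds the dose to 10 mg in a patient who tolerates more.

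Other points stand and limit the finding:

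- The warning in section 3 concerns long-term treatment of children in general. It names no dose and does not show that 11.4 mg is worse than 10 mg in a patient of 1.9 m².
- The affected group is narrow: above 1.67 m², tolerant of every step, and at full dose before 18. Patients must also still be in stage 0 or I at entry, which may be uncommon in late adolescence. The article gives no age distribution, so this is only an inference.
- A cap is a trade-off, because it lowers the dose per m² in the largest adolescents. The article does not establish that uniform dosing per m² is inferior to a flat cap.

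**Conclusion.** The concern holds as a minor one. As written, the under-18 ceiling exceeds the adult ceiling for any patient above 1.67 m². At assumed body surfaces of 1.8 to 2.0 m² the excess at full titration is 8% to 20%, followed by a reduction of 7% to 17% at 18 that is driven by age and not by tolerability.

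These sizes rest on the assumed body surfaces and on the patient tolerating the full 6 mg/m². The crossover at 1.67 m² rests only on the two stated limits. How many patients are affected cannot be computed, and the number may be small. Harm above 10 mg is not shown. An absolute limit may exist in the full protocol; the conclusion concerns the rule as published.

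**What to change.** Reword the under-18 sentence in section 2.3 to: *the maximum daily dose is the lower of 6 mg/m² and 10 mg, applied identically to ramipril and matching placebo.* This removes both the excess over the adult maximum and the forced cut at 18. Nothing changes at or below 1.67 m².

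The cost is one sentence, with no extra patients, visits or analyses. The downside is a somewhat lower top dose per m² in the largest adolescents: 10/1.8 = 5.6, 10/1.9 = 5.3 and 10/2.0 = 5.0 mg/m², instead of 6. If the sponsor has a reason to allow minors more than 10 mg, that reason should be stated beside the rule.

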### 2.4. Sample Size

The sample size/power calculation is driven by the primary efficacy endpoint, that is, the time to progression of Alport syndrome to the “next disease level” (Table 2). The proportions of patients who remain in one disease level during the study period of 3 years were estimated to be approximately 50% on placebo and approximately 80% on ramipril; that is, 50% of patients on placebo and 20% of patients on ramipril are expected to progress in disease level. This corresponds to a hazard ratio of 0.322. With a two-sided test at *α* level of 0.05, equal allocation to both groups, and an assumed hazard ratio of 0.322, the numbers of events of “next disease level” required to achieve a power of 80% and 90% are 24 and 33 [10], respectively. A sample size of 80 patients will provide 28 events within a fixed 3-year observation period (intervention time) and will therefore give a power in excess of 80%. Dropouts are unlikely in this population, because older relatives in these families are often severely affected—increasing the high degree of compliance towards a potentially renal-protective therapy in patients and parents.

The total time on ramipril is expected to be about 270 person-years with the patients randomized to ramipril contributing by 120 person-years (40 patients for 3 years), the open-label use by another 120 person-years (40 patients for 3 years), and the patients randomized to placebo who receive ramipril upon disease progression contributing by 30 person-years (estimated 20 patients with disease progression after an average of 1.5 years). Assuming a Poisson distribution of the events, this total length of followup is sufficient to estimate an adverse event rate of 1 in 10 person-years with a precision of 20%.

### 2.5. Trial Duration

Overall trial duration is expected to be 5.5 years with a recruitment period of 2 years, a treatment period of 3 years, and a follow-up period of 0.5 years. Trial duration for the individual patient is 3.5 years. Study start (recruitment) is planned for March 2012.

### 2.6. Outcome Measures

During the treatment period, safety and efficacy assessments take place every six months. Safety will be assessed by physical examinations, laboratory tests, vital signs, concomitant medications, and the recording of adverse events. Potential side effects of ramipril in adult patients with indications other than Alport syndrome are listed in detail in the product specification file. Briefly, significant side effects in adults include hyperkalaemia, hypotension, angioedema, acute renal failure, cataract, and hepatitis. Major adverse drug reactions are expected in less than 1% of the study participants. The risk of acute renal failure exists in cases of serious exsiccation (e.g., as a result of serious diarrhoea). This correlation will be explained to patients and to their parents/legal guardian, respectively, in order to avoid the risk of acute renal failure. Efficacy will be assessed by laboratory tests (blood, urine), height, and weight. Additional serum and urine samples will be taken for the development of serum and urinary markers of renal disease progression (exploratory). A blood sample for DNA extraction may be taken if indicated to confirm the patient's Alport mutation (genetic testing is not part of this study). After completion of the treatment period, patients will be advised to undergo a hearing test and an eye examination.

### 2.7. Statistical Analysis

The primary efficacy endpoint “time to progression to the next disease level” for randomized patients will be assessed in 6-monthly intervals over the treatment period of 3 years. A proportional hazards' model for interval-censored data will be applied with effects for treatment, trial site, and proteinuria at start of therapy. If indicated, additional potentially confounding variables such as genotype and age will be added to the model. An estimate of the treatment effect is reported in terms of the hazard ratio with 95% confidence interval and *P* value testing the null hypothesis of no effect.

The primary safety endpoint is the “incidence of adverse drug events (ADE), for example, angioedema, acute renal failure, hyperkalemia, under ramipril treatment before disease progression compared to placebo before disease progression, for all randomized patients.” The incidence rates will be analyzed using a generalized linear model with log link (Poisson regression) and corrected, if necessary, for overdispersion due to interpatient heterogeneity. An estimate of the treatment effect is reported in terms of the rate ratio with 95% confidence interval and *P* value testing the null hypothesis of no effect.

The secondary efficacy endpoint “albuminuria after 3 years corrected for baseline albuminuria for patients randomized to receive ramipril compared to placebo” will be analyzed by means of an analysis of covariance (ANCOVA) with treatment, trial site, and proteinuria at start of therapy as factors and baseline albuminuria as covariate. The treatment effect estimate in terms of a mean difference will be reported with 95% confidence interval and *P* value testing the null hypothesis of no treatment effect. The *secondary safety endpoint* “incidence of ADEs during 3 years of treatment for patients randomized to receive ramipril compared to placebo” will be carried out in the same way as the primary safety analyses described above. Other secondary end points include eye involvement and hearing loss. Results will also be stratified by age groups. No interim analyses are planned.

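### On the article's own definitions, the only baseline disease term in the primary model is constant or nearly so; replace it with Alport stage or log baseline albuminuria

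*Protocol article*

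**What the plan says.** Section 2.7 fits a proportional hazards model for interval-censored data with "effects for treatment, trial site, and proteinuria at start of therapy". It continues: "If indicated, additional potentially confounding variables such as genotype and age will be added to the model". The ANCOVA for the secondary efficacy endpoint is specified "with treatment, trial site, and proteinuria at start of therapy as factors and baseline albuminuria as covariate".

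Table 1 defines Stage II as "Proteinuria >300 mg albumin/gCrea" and calls the band from 30 to 300 mg/g (Stage I) microalbuminuria. Table 3 excludes "Alport syndrome stages II, III, or IV". Section 2.2 describes the population as "before proteinuria >0.3 g per day".

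Under Section 2.1, randomised patients are in Stage 0 or I at screening, and randomisation is stratified by trial site only. Table 2 sets one progression rule for patients who start in Stage 0 and another for those who start in Stage I.

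**The concern.** The term meant to carry baseline disease severity in the primary model is named after a condition that the eligibility criteria rule out. A factor with a single level cannot be estimated and drops out, leaving treatment and site.

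This matters more here than in most trials because the event itself is defined relative to baseline albuminuria, with a different rule for each stage. Stage is not balanced by design either. With 80 patients and 28 expected events, a baseline variable tied to the event rule is worth having in the model, and the data for it are already collected.

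**Working it through.** **1. The plan's own figures.** Hazard ratio: ln(0.8)/ln(0.5) = 0.322, as stated. Required events by Schoenfeld's formula, with |ln 0.322| = 1.133: (1.960 + 0.842)²/(0.25 × 1.133²) = 24.4 for 80% power, and (1.960 + 1.282)²/(0.25 × 1.133²) = 32.7 for 90%. The article gives 24 and 33. Expected events: 40 × 0.5 + 40 × 0.2 = 28. Power at 28 events: Φ(√28/2 × 1.133 − 1.960) = 85%. The sample-size statement holds and this point does not affect it.

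**2. Does the term vary?**
- Table 1: proteinuria means more than 300 mg/g.
- Table 3: nobody at or beyond that stage is eligible.
- Section 2.7, ANCOVA: proteinuria is listed among the factors, and baseline albuminuria separately as covariate. This suggests a category rather than a measured level.

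On these terms the factor is absent for every randomised patient, except any who cross 300 mg/g between screening and start of therapy. Hence constant or nearly so.

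**3. Does the event rule depend on stage?** Take the two Stage I criteria in Table 2 as alternatives. The rise needed to count as progression is then max(3, 30/baseline)-fold in Stage 0 and min(2, 300/baseline)-fold in Stage I. For illustrative baselines:

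| Baseline, mg/g | Stage | Rise needed |
|---|---|---|
| 5 | 0 | 30/5 = 6-fold |
| 20 | 0 | 3-fold |
| 40 | I | 2-fold |
| 200 | I | 300/200 = 1.5-fold |

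This shows that the hurdle differs. It does not show how much the hazard differs, and the article gives no progression rate by stage.

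**4. Illustrative effect on power.** Assumptions not in the article: half the patients in Stage I, a constant stage hazard ratio k, no dropout and no site effects. Progression times are grouped at 6 months, with 40 patients per arm. The placebo hazard λ solves ½e^(−3λ) + ½e^(−3λk) = 0.5. Two calibrations were simulated.

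*A. Within-stage treatment hazard ratio held at 0.322* (1,000 runs; Cox model with Efron ties in place of the interval-censored model):

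| k | Power without / with stage | Median HR without / with stage |
|---|---|---|
| 1 | 82% / 82% | 0.31 / 0.31 |
| 2 | 81% / 84% | 0.33 / 0.32 |
| 4 | 78% / 84% | 0.34 / 0.31 |
| 6 | 72% / 83% | 0.36 / 0.31 |

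*B. Overall progression held at 50% and 20%* (2,500 runs; grouped proportional hazards model):

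| k | Power without / with stage |
|---|---|
| 1 | 82% / 81% |
| 2 | 82% / 84% |
| 3 | 82% / 86% |
| 5 | 84% / 90% |

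The calibrations differ for a simple reason. For k = 2, placebo survival in Stage 0 solves x + x² = 1, so x = 0.618. Under A, ramipril progression is 1 − ½(0.618^0.322 + 0.382^0.322) = 20.5%, and the same sum gives 23.1% at k = 6, so the overall contrast weakens. Under B, y + y² = 1.6 gives y = 0.860 and a within-stage hazard ratio of ln 0.860/ln 0.618 = 0.313, so it is the within-stage effect that strengthens.

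The Monte Carlo standard error of one power figure is √(0.8 × 0.2/1000) = 1.3 points for A and √(0.8 × 0.2/2500) = 0.8 points for B.

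**5. Chance imbalance.** Under simple 1:1 allocation, the hypergeometric probability that the arms differ by 15 points or more in Stage I share (6 patients in 40) is 26% if 40 of the 80 are in Stage I, and 20% if 20 of the 80 are.

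**The case against.** The strongest reply is that the constancy rests on one reading. Table 1 and Section 2.2 both attach a threshold to proteinuria, and the discussion speaks of overt proteinuria, which leaves room for a lower grade. If the term means a measured protein level, or microalbuminuria yes or no, it varies among eligible patients and stands in for stage. That is fair, and non-estimability is not proven. But on that reading the term departs from Table 1's vocabulary and still needs replacing.

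Some stronger inferences are tempting, and the article does not support them:
- **That the ANCOVA also lacks stage adjustment.** It carries baseline albuminuria, the quantity that separates Stages 0 and I in Table 1. There the proteinuria factor is at worst redundant.
- **That start of therapy has no meaning for placebo patients.** Sections 2.1 and 2.3 describe study treatment in both arms, so the phrase naturally means the start of study treatment.
- **That stage is the leading predictor of progression.** No passage gives progression by stage or ranks predictors. The stage-specific event rule is reason enough to adjust.
- **That the clause on genotype and age inflates the type I error by a known amount.** Nothing says the choice is made unblinded or by the treatment P value, and the rule may stand in the full protocol or SAP, which are not shown. A best-of-several calculation would only bound an unseen rule.

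It is also fair that the power gains rest on an assumed stage mix and assumed hazard ratios, and that stratifying by site alone is a legitimate choice in a small multicentre trial.

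**Conclusion.** The point holds as a correction to one model term. In the article's own vocabulary the proteinuria factor is constant or nearly so, which leaves the primary model without adjustment for Stage 0 versus I. On the looser reading the term is undefined and clashes with Table 1. Either way it should be replaced.

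A reader might infer that the primary test is invalid. It is not: randomisation protects it. What is lost is efficiency, with some attenuation of the hazard ratio and no correction for chance imbalance. With half the patients in Stage I and a stage hazard ratio of 2 to 5, the gain from adding stage is roughly 2 to 6 points of power. Unadjusted power falls below the planned 80% only under calibration A, at stage hazard ratios of about 4 or more. With no stage effect, the 1-point difference or less is within simulation error.

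**What to change.** - **Primary model.** Replace the proteinuria term by one baseline disease term, named in advance: Alport stage (0 or I) or log baseline albuminuria. Do not enter both. Stage is a cut of albuminuria, and about 28 expected events already have to support the site effects.
- **ANCOVA.** Drop the proteinuria factor or replace it by stage. Keep baseline albuminuria as covariate.
- **Genotype and age (secondary point).** Decide before unblinding whether each is in the primary model, and report other covariate sets as sensitivity analyses. If the full protocol or SAP already does this, a reference to it is enough.

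The cost is wording in Section 2.7 and the SAP. Both candidate variables follow from baseline albuminuria, which eligibility and Table 2 already require, so no new data, patients or visits are needed. The one thing given up is the freedom to choose covariates for the primary model later.
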